## Materials and Methods

*Study setting*

The study will be conducted among 12 year old school children of Mangalore, India. 

*Broad objective:*

To contribute toward national efforts to protect children from harmful effects of SHS, the objective of this study is to develop effective school-based intervention to reduce exposure and improve adolescents’ knowledge and attitude towards Second Hand tobacco Smoke and to promote smoke free homes.

*Specific objectives*

To assess exposure to second hand tobacco smoke among 12 year old school children.

To carry out a school based ‘*tobacco free*’ educational intervention program among 12 year old school children.

To assess the Salivary Cotinine level as well as the knowledge, attitude and avoidance behaviour towards second hand tobacco smoke among 12 year old school children, before and after carrying out an intervention. 

*Study design and registration*

This will be a multiphase study using multiphase sampling technique among adolescents in Mangalore, India. The first phase will be a descriptive cross-sectional study. A cluster random sampling of all the schools in Mangalore will be done to obtain the required sample size of 1400. A questionnaire will then be administered to the 12 year olds in the selected schools, who fulfil the inclusion criteria. Data will be analysed and those students who report exposure to second hand tobacco smoke will be selected and their salivary cotinine level checked until we get a sample of 250 subjects with salivary cotinine levels of > 0.1 ng/mL (Avila-Tang et al., 2012). These will form the sample for the second phase of the study which will be a randomized controlled trial. (Figures 1 and 2). 

The protocol follows SPIRIT guidelines (Chan et al., 2013) and includes all items from the World Health Organization Trial Registration Data Set (WHO., 2019) [Appendix 1]. The trial has been registered with the Clinical Trial Registry of India (CTRI) with number CTRI/2018/09/015706 (Registered on 13/09/2018).

*Sample size calculation*

*For phase 1: (Cross-sectional study)*

The sample size estimation was done using the formula:

$n=\frac{{\left(Z_{1-a/2}\right)}^{2}\mathrm{PQ}}{d^{2}}$

where: 

Z_1-α/2_ = 1.96 (when α is 5% at 95% confidence limits)

P= Proportion of the event in the population (29%) (Singh et al., 2011)

Q=1-P (0.71)

d= Acceptable margin of error (3%)

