With a design effect at 1.5 and a non-response at 5%, the final sample size was calculated to be 1400 for the Phase 1 study.

*For phase 2: (Randomized controlled trial)*

The sample size calculation for Phase 2 randomized controlled trial was done using G Power 3.1.2. We calculated a total sample size of 250 with125 in the control group and 125 in the intervention group, 90% power, an Effect size of 0.3, confidence interval at 95% and attrition at 10%.

*Recruitment and eligibility*

The study is now recruiting and the criteria for eligibility are as follows, 

*Inclusion criteria for phase 1 study *

1. All Schools in Mangalore who have primary and secondary schools in the same campus.

2. Those schools who consent to participate in the study

3. Students whose parents give written informed consent and they themselves give informed assent.

*Exclusion criteria for phase 1 study*

1. Participants who are self-reported smokers.

*Inclusion criteria for phase 2 study *

1. Inclusion criteria: Participants with salivary cotinine levels of > 0.1 ng/mL

2. Exclusion criteria: Participants whose sibling is already a participant in the study

*Study procedure*

*Phase 1*

The first phase will be a descriptive cross-sectional study. A cluster random sampling of all the schools in Mangalore will be done to obtain the required sample size of 1,400. A questionnaire will then be administered to the 12 year olds in the selected schools, who fulfil the inclusion criteria. 

*Questionnaire*

Demographic data will be recorded. Socioeconomic status will be assessed using the BG Prasad Scale (Prasad., 1961) modified considering the base of Consumer Price Index (CPI) for 2017 (Singh et al., 2017). The questionnaire will have two components, one to assess children’s exposure to SHS using Questionnaire 1 which has 5 questions (Lin et al., 2010). The second component, Questionnaire 2, is a 25 item questionnaire (Gharaibeh et al., 2011) to determine Children’s knowledge, attitude and behaviour towards second hand smoke. Knowledge will be assessed using 10 items, Attitude with 5 items, Avoidance behaviour towards second hand smoke will be assessed using 5 items and Self-efficacy of avoidance will be assessed using 5 items. This assessment will be carried out at the start of Phase 1 and at all 3 follow-up time points in Phase 2.

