The intervention consists of 40 min ‘tobacco free’ health education session delivered once a week for 3 consecutive weeks by the principal investigator (PI) (AR). The first session will address tobacco and its adverse effects. The second session will be on laws regarding tobacco in India and the World and the third session will be on how to prevent exposure to tobacco. Teaching methods include lectures, demonstrations, discussions, storytelling and quiz. Children are also given take home brochures every week that contains messages on the effects of tobacco and how to make their homes smoke-free.

There will be 3 follow up time points. The first follow up will be at the 3rd month, second follow up at the 6th month and the third follow up at 12 months after the intervention. On the first day of each follow up, the PI will reinforce the key points of the intervention and also discuss with the students regarding their experiences at home and the challenges they faced. The timeline is given in Appendix 2. Participants in the control arm will receive conventional standard health education once, whereas those who report tobacco use will be encouraged to participate in tobacco counselling.

*Study outcomes*

To assess if there is any change in the salivary cotinine levels and the knowledge, attitude and behaviour scores of the participants after a ‘tobacco free’ health educational intervention.

To develop effective school-based intervention to reduce exposure and improve adolescents’ knowledge and attitude towards Second Hand tobacco Smoke and to promote smoke free homes.

*Data analysis plan*

Analysis will be done based on both the Intention to Treat and Per Protocol analysis. The data will be entered into the SPSS software (IBM Corp. Released 2011. IBM SPSS Statistics for Windows, Version 20.0. Armonk, NY: IBM Corp.) and analysed. Descriptive statistics will be presented and sub group analysis will be done wherever needed. The level of significance will be kept at 0.05 with 95% confidence levels. For the phase 1 study, Chi square test will be done for categorical variables and Independent sample t test will be done to compare means. Logistic regression will be done to obtain the adjusted odds ratio. For the phase 2 study, Paired sample t - test will be done.

*Ethical aspects*

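### Phase 1 is sized as a cluster sample of schools, but the tests named for it treat pupils as independent, so results for school-clustered predictors will be too optimistic

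*Protocol article*

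**What the plan says.** The only document at hand is the protocol article. Under Materials and Methods it says three things that bear on this point.

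- **Sampling.** Schools are the sampling unit in Phase 1: "A cluster random sampling of all the schools in Mangalore will be done".
- **Size.** The sample size section uses the single-proportion precision formula with an expected proportion of 29% and a margin of 3 points, and then allows for clustering: "With a design effect at 1.5 and a non-response at 5%, the final sample size was calculated to be 1400 for the Phase 1 study".
- **Analysis.** The data analysis plan states: "For the phase 1 study, Chi square test will be done for categorical variables and Independent sample t test". The t test is for comparing means. It adds: "Logistic regression will be done to obtain the adjusted odds ratio". The significance level is 0.05 with 95% confidence.

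The article nowhere mentions a school term, a mixed model, generalised estimating equations, cluster-robust variance or a complex-samples procedure.

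**The concern.** The sizing accepts that pupils of one school resemble each other and pays for it with half as many pupils again. The named tests, in their usual form, then treat every pupil as a separate piece of information. The design and the analysis therefore rest on different assumptions about the same data.

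What is at stake is how Phase 1 is reported. Measuring second-hand smoke exposure is the first specific objective, and adjusted odds ratios are a stated output. Standard errors that ignore clustering can be too small. Associations with factors that differ between schools could then be called significant too often, and the prevalence could look more precise than it is. Socioeconomic status, which is recorded, may be such a factor, although the article does not show how strongly it clusters by school.

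**Working it through.** **Inputs from the sample size section:** z = 1.96, P = 0.29, Q = 0.71, d = 0.03, design effect (DEFF) 1.5, non-response 5%, stated N = 1400.

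**1. Reproduce the plan's figure.**
- n0 = z²PQ/d² = 1.96² × 0.29 × 0.71 / 0.03² = 878.9
- With clustering: 878.9 × 1.5 = 1318.3
- With non-response: 1318.3 / 0.95 = 1387.7, which agrees with 1400 after rounding up.
- Without the design effect: 878.9 / 0.95 = about 925.

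The 1400 is therefore sound, and it is reached only by counting on within-school correlation.

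**2. Prevalence, if the interval ignored clustering.** With 5% non-response, 1400 × 0.95 = 1330 pupils respond.
- Half-width ignoring clustering: 1.96 × √(0.29 × 0.71 / 1330) = 0.0244, or 2.4 points.
- Half-width allowing for DEFF 1.5: 0.0244 × √1.5 = 0.0244 × 1.225 = 0.0299, or 3.0 points, which is the planned margin.
- Coverage of the naive 95% interval: 1 − 2 × [1 − Φ(1.96/√1.5)] = 1 − 0.110 = about 89%.

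**3. Tests of association.** The 1.5 was set for a single proportion. For a comparison, the variance inflation also depends on how strongly the predictor clusters by school. If the outcome has a design effect of 1.5, the inflation is roughly 1 + 0.5 × ρx, where ρx is the within-school correlation of the predictor. The true type I error of a naive 5% test is 2 × [1 − Φ(1.96/√inflation)]. The article gives no ρx, so the values below are assumptions.

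| ρx (assumed) | Variance inflation | Type I error |
|---|---|---|
| 0.05 | 1.025 | 5.3% |
| 0.1 | 1.05 | 5.6% |
| 0.2 | 1.10 | 6.2% |
| 1 (constant within school) | 1.50 | 11.0% |

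For a factor that is balanced within schools, such as perhaps sex, the direction can even reverse.

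**4. Sensitivity to the design effect.** The article gives neither the number of schools, nor pupils per school, nor the intraclass correlation, so the design effect that will be observed is unknown. Over an assumed range, and for a predictor constant within school:
- DEFF 1.25: type I error 8.0%. A naive prevalence interval would cover 92.0%.
- DEFF 2.0: type I error 16.6%. A naive prevalence interval would cover 83.4%.

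**The case against.** The strongest reply has three parts.

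**The article is condensed.** It names families of tests in two sentences, and variance estimation is commonly left to an analysis plan that is not shown. Logistic regression is compatible with a cluster adjustment. This lowers certainty about what will finally be done. It does not remove the point, because the article has its own data analysis section and commits there to named tests. The independent-samples t test in particular reads as the standard procedure. An analysis plan that followed this text would carry the conflict forward.

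**The size is easily overstated.** A reader might infer that every Phase 1 test understates the variance by a factor of 1.5, so that all nominal 5% tests reject about 11% of the time. The document does not support that. The 1.5 belongs to one proportion, and the 11% needs a predictor that is constant within school. The article itself describes the home as the main source of exposure, so many natural predictors are child or household factors, for which the error may be close to nominal. A reader might also infer that the prevalence will certainly be reported too precisely. No method for that interval is stated, and the sizing does allow for clustering. Both parts of this objection stand.

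**Phase 1 is descriptive.** Pupils enter Phase 2 through reported exposure and a cotinine threshold, not through a Phase 1 p-value or interval. This also stands, and it limits the severity.

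**Conclusion.** The conflict is real and lies in what the plan states: a cluster sample, sized as one, is paired with tests that in their ordinary form assume independent pupils. If those tests are applied as written, p-values and intervals will be too optimistic for school-level or strongly school-clustered predictors. At the plan's own design effect, type I error is at most about 11%, and it is near 5% for predictors that vary mainly within schools. These figures assume that the outcome of the comparison has a design effect of 1.5. The prevalence figures (2.4 against 3.0 points, about 89% coverage) are conditional on an interval that ignores clustering, which the plan does not specify.

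The severity is moderate. The sample size of 1400 is not in question, the prevalence point estimate does not depend on the choice of test, and this point does not touch the Phase 2 treatment comparison.

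**What to change.** State in the data analysis plan that Phase 1 is analysed with school as the primary sampling unit:

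- a design-based confidence interval for exposure prevalence;
- the Rao-Scott chi-square in place of the ordinary one;
- linear and logistic models with a random school effect or cluster-robust variance, with a small-sample correction if there are few schools;
- the observed intraclass correlation and design effect in the report.

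The Phase 1 intraclass correlation should not be carried into Phase 2 as a planning value. Exposure among all sampled pupils is a different outcome in a different population from 12-month cotinine among pupils selected for a level above 0.1 ng/mL.

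**Cost.** No extra pupils are needed, and the change can be made at analysis as long as school is recorded. It takes revised wording and a little more analysis work. Prevalence intervals become about 22% wider than naive ones at a design effect of 1.5 (√1.5 = 1.225), which brings them to the planned 3-point margin. With few schools, the small-sample correction would widen them further.

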The questionnaire will be administered to 10 individuals and reliability measured using the Cronbach’s coefficient alpha. A high coefficient indicates that the items are consistently measuring the same underlying construct.

Data will be analysed and those students who report exposure to second hand tobacco smoke will be selected and their salivary cotinine level checked.

*Salivary Cotinine level estimation*

Children’s exposure to SHS will be determined by measuring their salivary cotinine levels twice, one at the end of Phase 1(baseline) and second at the 3rd follow-up, i.e., at 12 months after the intervention. Salivary cotinine is a sensitive biochemical marker which is strongly associated with exposure to SHS. It has a half-life of 16 hours and is a widely recognized marker for detecting both active and passive smoking. 

Saliva collection: Saliva will be collected not before at least 60 minutes after a major meal. Participant will be asked to rinse mouth thoroughly with water 10 minutes before sample is collected. The head is tilted forward, allowing the saliva to pool on the floor of the mouth. Whole saliva will be collected in a labelled vial by unstimulated passive drool. After collection, sample will be refrigerated within 30 minutes, and frozen at or below -20ºC within 4 hours of collection. 

Salimetrics^®^ High Sensitivity Salivary Cotinine Quantitative Enzyme Immunoassay Kit will be used for cotinine estimation in saliva (Salimetrics., 2018). There will not be any personal identifiers on the vials sent to the laboratory and individual results will not be disclosed.

The participants who have salivary cotinine levels of > 0.1 ng/mL will be selected and they will form the sampling frame for the second phase of the study which will be a randomized controlled trial.

*Phase 2*

This phase will be a randomized controlled trial, with a sample size of 250, 125 participants in the intervention group and 125 in the control group.

Random allocation: Sequence generation will be done using the table of random numbers. We will adopt the process of first identifying potential individual participants in each cluster, recruiting these participants and then do cluster randomisation. Allocation concealment will be done using sequentially numbered, opaque, sealed envelopes (SNOSE). The study will be outcome assessor blinded.

*Intervention*

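### Phase 2 names only a paired t-test, so baseline cotinine and scores enter by subtraction within an arm; the intervention effect should come from a baseline-adjusted comparison between arms

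*Protocol article*

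**What the plan says.** The protocol article, under Data analysis plan, lists chi-square tests, independent t-tests and logistic regression for Phase 1, then closes with a single sentence for the trial: "For the phase 2 study, Paired sample t - test will be done". The adjusted odds ratio is mentioned within the Phase 1 list. No covariate is named for Phase 2.

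The baseline data exist for every child in the trial. Under Salivary Cotinine level estimation, exposure is determined by "measuring their salivary cotinine levels twice, one at the end of Phase 1(baseline) and second at the 3rd follow-up", which is the 12-month visit. A baseline cotinine above 0.1 ng/mL is also the entry criterion for Phase 2. For the knowledge, attitude, avoidance and self-efficacy items, the Questionnaire section says "This assessment will be carried out at the start of Phase 1 and at all 3 follow-up time points in Phase 2".

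Study outcomes frames the aim as change: "To assess if there is any change in the salivary cotinine levels and the knowledge, attitude and behaviour scores of the participants". Under Random allocation, participants are recruited first and the clusters are then randomised.

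**The concern.** A paired t-test asks whether the mean follow-up value differs from the mean baseline value in one group of children. The trial asks whether the two arms differ after the intervention. The obvious repair is to compute each child's change and compare the mean changes between arms. That would answer the right question but still use the baseline poorly.

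Subtraction fixes the coefficient of baseline at 1. The most efficient coefficient is the within-arm regression slope, rho × SD(follow-up)/SD(baseline), which equals rho when the two SDs are equal. Several features of this trial make a modest rho plausible for cotinine: the readings are a year apart, the stated half-life of the marker is 16 hours, and children are selected on the baseline reading itself.

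Two things are at stake once the arms are compared: precision, in a trial of only 125 per arm, and the handling of chance baseline differences, which are larger under cluster randomisation than under individual randomisation. With change scores, the arm that starts higher by chance tends to show the larger fall, which can imitate or mask an effect.

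**Working it through.** **Inputs from the article.** Sample size: "We calculated a total sample size of 250 with125 in the control group and 125 in the intervention group". Planning values: "90% power, an Effect size of 0.3, confidence interval at 95% and attrition at 10"%. Significance level 0.05, taken as two-sided. Ten per cent attrition leaves 125 × 0.9 = 112.5, so about 112 per arm.

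**Inputs not in the article (assumed).** The within-arm correlation rho between baseline and follow-up; the SDs at the two times; the meaning of the effect size 0.3; the number of clusters and the intraclass correlation.

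**1. The plan's own figure.**
- Two-sample t-test, 0.3 as a between-arm standardised difference, 90% power, two-sided: 235 per arm, or 235/0.9 = 262 with attrition. This does not give 125.
- Paired t-test within one arm, 0.3 as mean change over the SD of change: 119, or 119/0.9 = 133 with attrition. This does not give 125 either, but power is 91.4% at 125 and 88.2% at 112.

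The stated size is not reproduced. It is closest to a within-arm paired calculation. Reading 0.3 as a between-arm difference in the steps below is therefore an assumption.

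**2. Variance of the two comparisons.** Take the follow-up SD as 1 and the baseline SD as equal to it.
- Change score: variance 2(1 - rho).
- Baseline-adjusted: variance 1 - rho².
- Ratio of adjusted to change: (1 - rho²)/[2(1 - rho)] = (1 + rho)/2, that is 0.65, 0.75, 0.85 and 0.90 at rho 0.3, 0.5, 0.7 and 0.8.

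**3. Power if the arms were compared.** Power is approximately Φ(0.3·√(n/2)/SD - 1.96), clustering ignored. At n = 125 and rho 0.5, √62.5 = 7.906. The change score has SD 1, so 0.3 × 7.906 = 2.372 and the power is 66.0%. The adjusted SD is 0.866, so 2.372/0.866 = 2.739 and the power is 78.2%.

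| rho | Change, n = 125 | Adjusted, n = 125 | Loss (points) | Change, n = 112 | Adjusted, n = 112 |
|---|---|---|---|---|---|
| 0.3 | 51.8% | 70.1% | 18 | 47.5% | 65.3% |
| 0.5 | 66.0% | 78.2% | 12 | 61.2% | 73.6% |
| 0.7 | 86.5% | 91.3% | 5 | 82.6% | 88.2% |
| 0.8 | 96.3% | 97.7% | 1 | 94.4% | 96.3% |

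**4. Unequal SDs.** With k = SD(baseline)/SD(follow-up), the change variance is 1 + k² - 2·rho·k; the adjusted variance stays 1 - rho². At rho 0.5 and 125 per arm:
- k = 0.7: variance 0.79, power 76% against 78%.
- k = 0.8: variance 0.84, power 73% against 78%.
- k = 1.2: variance 1.24, power 57% against 78%.

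So at this one rho the loss runs from about 2 to 21 points.

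**5. Clustering.** At rho 0.5 and 125 per arm, dividing n by an assumed design effect of 1.5, 2 or 3 gives 49% against 61%, 39% against 49%, and 28% against 35%. The gain shrinks from 12 to about 7.5 points but remains.

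**6. Chance baseline difference.** With equal SDs, a baseline difference D between arms moves the change-score estimate by -(1 - rho)D. For D = 0.2 SD this is -0.14, -0.10 and -0.06 SD at rho 0.3, 0.5 and 0.7. At 0.5 that is a third of 0.3. The SD of D is √[(2/125)(1 + (m - 1)·ICC)]. With an assumed ICC of 0.05, 5 clusters of 25 per arm give √(0.016 × 2.2) = 0.19, and 10 clusters of 12.5 give √(0.016 × 1.575) = 0.16. A difference of 0.2 would then be unremarkable.

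**The case against.** The strongest reply is that the article does not contain the comparison being criticised. A reader might infer that the plan as written gives up about 12 points of power and leaves baseline differences in its effect estimate. The document does not support that. A within-arm paired test produces no between-arm estimate, so it has no between-arm power to lose and no estimate for imbalance to distort. The 12 points apply only if arms are compared on change scores, a method the article never names, and then only at rho 0.5 with equal SDs. Nor would subtraction leave a baseline difference untouched; it over-corrects it. This part of the reply stands in full.

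It can also be said that a condensed article leaves covariates to a fuller document. That would answer silence, but here a specific method is stated, and that method cannot take a covariate. A fuller plan would have to replace it.

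Two further cautions stand. Step 6 applies an individual-level rho to differences that partly reflect clusters. If cluster differences persist over the year, they carry over more strongly and the residual is smaller. And under randomisation the shift is conditional on the imbalance that occurred; it is not a bias on average.

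Lastly, the absence of any between-arm comparison and of any allowance for clusters is the larger defect in the same sentence. That is true, but a sponsor told only to compare the arms could well compare paired changes, so the role of baseline is worth fixing at the same time.

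**Conclusion.** The point holds in a conditional form. The one Phase 2 method stated uses baseline by subtraction within an arm, and the data for a better analysis are already planned. If the arms were compared on paired changes, the variance would exceed that of a baseline-adjusted comparison for every rho below 1 under equal SDs. The power loss at 125 per arm would be about 18, 12, 5 and 1 points at rho 0.3, 0.5, 0.7 and 0.8. These figures assume that 0.3 is a between-arm standardised difference, that the test is two-sided at 0.05, that the SDs are equal, and that there is no clustering. None of the four is stated outright in the article, and the last does not fit the cluster design, so the figures are a range for illustration and not a measured cost of the plan. The over-correction of about (1 - rho) times a chance baseline difference is subject to the same limits.

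**What to change.** In the Phase 2 part of the data analysis plan, replace the paired t-test as the basis for the intervention effect. State that each outcome's effect will be estimated by regressing the follow-up value on arm and on that outcome's own baseline value, in a model that accounts for the randomised clusters: 12-month cotinine on baseline cotinine, and each 3-, 6- and 12-month score on the corresponding score from the start of Phase 1. Keep within-arm paired changes as descriptive summaries only.

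The covariate uses data already being collected, with no extra visit or participant. It costs one degree of freedom per outcome and slightly more analysis work. It does not by itself make the analysis valid; the between-arm comparison and the cluster structure have to be written into the same model.

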**Design::**

A multiphase study with a descriptive cross-sectional questionnaire phase 1 and a phase 2 cluster randomized controlled trial (RCT), conceptualized to determine the effectiveness of a school-based ‘tobacco free’ health education intervention on adolescents’ knowledge and attitude towards SHS.

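### The only Phase 2 test named is a paired t-test, which measures change within an arm and never compares the randomised arms

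*Protocol article*

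**What the plan says.** The Design paragraph of the abstract describes "a phase 2 cluster randomized controlled trial (RCT), conceptualized to determine the effectiveness of a school-based" intervention. Under Random allocation, individual children are identified first, with the investigators "recruiting these participants and then do cluster randomisation". The control arm gets standard health education once.

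The Data analysis plan assigns tests by phase. For the survey: "For the phase 1 study, Chi square test will be done for categorical variables and Independent sample t test will be done to compare means", with logistic regression for adjusted odds ratios. For the trial: "For the phase 2 study, Paired sample t - test will be done". On populations it adds: "Analysis will be done based on both the Intention to Treat and Per Protocol analysis". Under Study outcomes, the aim is worded as change after the intervention, with no mention of a comparison with control.

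Entry to Phase 2 is set by "Inclusion criteria: Participants with salivary cotinine levels of > 0.1 ng/mL". The section on salivary cotinine estimation schedules two measurements only: one at the end of Phase 1, labelled baseline, and one at 12 months. The qualifying value is therefore also the baseline value.

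The sample size section states "We calculated a total sample size of 250 with125 in the control group and 125 in the intervention group", with 90% power, an effect size of 0.3 of unstated type, and 10% attrition.

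**The concern.** A paired t-test on before and after values asks whether the mean change within one group is zero. It makes no use of the control arm, so it cannot separate the effect of the intervention from whatever would have happened anyway. The article does name a between-group test, but gives it to the descriptive survey and not to the trial.

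Two sources of common change are plausible here. Questionnaire scores can move as children grow older and answer the same items again. Cotinine can fall because children enter on a single value above a cut-off, and that same value serves as baseline; re-measurement then tends back towards the source mean in both arms. If the plan is followed as written, such a change could be reported as an effect of the programme, and the question the trial was randomised to answer would have no stated test.

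**Working it through.** **1. Is there any between-arm test for Phase 2?** The chi-square test, independent t-test and logistic regression are all placed under Phase 1. Intention to treat and per protocol say who is analysed, not which contrast is tested. No matching of clusters or children is described that would turn a paired test into a comparison of arms. So none is named.

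**2. The plan's own figure.** Inputs from the sample size section: effect size 0.3, 90% power, 10% attrition, total 250. Alpha is 0.05 (Data analysis plan); two-sided is assumed. Completers: 125 × 0.9 = 112.5, taken as 112.
- Two independent means: n per arm = 2 × ((1.960 + 1.282)/0.3)² = 233.5, so 234; total 468; 468/0.9 = 520.
- Paired, within one arm: n = ((1.960 + 1.282)/0.3)² = 116.8, so 117 (119 by exact t); 129 to 133 with attrition, or 258 to 266 for two arms.
- One-sided versions with attrition give about 425 (two-sample) and 212 to 216 (paired, two arms). ANOVA with f = 0.3 gives 119 in total.

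None gives 250 within 3%. Two-sided power at the planned size:

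| Test, effect 0.3 | 112 per arm | 125 per arm |
|---|---|---|
| Paired, within one arm | 88% | 91% |
| Unadjusted between arms | 61% | 66% |

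Between arms with 112: Φ(0.3 × √(112/2) − 1.96) = Φ(0.285) = 0.61. With 125: Φ(0.3 × √(125/2) − 1.96) = Φ(0.412) = 0.66.

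**3. Regression to the mean, log cotinine.** Assumptions, none given in the documents: log cotinine is normal with SD 1 at both times, the intervention has no effect, the baseline to 12-month correlation ρ is 0.4 to 0.8, and a share p of tested children exceeds the cut-off c. The lower value of p is 250/(0.29 × 1400) = 250/406 = 0.62. This borrows the 29% from the Phase 1 sample size and treats it as the share reporting exposure, in which case it is the lowest share that still fills the trial. The upper value of p is 0.90.

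Expected fall = (1 − ρ) × φ(c)/p. SD of change = √((1 − ρ)² × Var(X | X > c) + 1 − ρ²). The standardised paired effect dz is their ratio; power comes from the noncentral t at n = 112.

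For p = 0.62: c = −0.305, φ(c)/p = 0.614, Var = 0.435. At ρ = 0.6: fall = 0.4 × 0.614 = 0.246; SD = √(0.16 × 0.435 + 0.64) = 0.842; dz = 0.292; probability of significance 86%.

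| Share above cut-off | ρ = 0.4 | ρ = 0.6 | ρ = 0.8 |
|---|---|---|---|
| 62% | 97% | 86% | 55% |
| 70% | 87% | 69% | 39% |
| 80% | 57% | 40% | 22% |
| 90% | 22% | 16% | 10% |

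**4. The same on untransformed cotinine.** The article mentions no log transformation. Simulating lognormal cotinine with an assumed log SD of 0.7 to 1.4, n = 112 and ρ from 0.4 to 0.8, the paired test is significant in about 5% to 53% of trials at a share of 62%, and in about 4% to 8% at 90%. Greater skewness brings the figure down towards nominal.

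**5. Power of a corrected analysis.** With 112 per arm, baseline adjustment multiplies the SD by √(1 − r²). Assumed r of 0.3, 0.5 and 0.7 gives 65%, 74% and 88%, before clustering. If the Phase 1 design effect of 1.5 also applied to Phase 2, the effective n would be 112/1.5 = 74.7 per arm and unadjusted power about 45%.

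**The case against.** The strongest defence is that a journal article condenses the plan, and that a between-arm model may sit in an analysis plan not shown. That would answer an omission. Here the article makes a choice: it allots tests by phase and gives the trial only the within-arm one.

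The case against a large figure is better and mostly stands. A reader might infer that selection alone will produce a significant fall in most trials, since 86% appears at ρ = 0.6. That value needs log cotinine, which the plan does not state, and the lowest share that fills the trial. At a share of 90% on the untransformed scale the test is close to nominal. Nor do the documents say that cotinine will fall or scores will rise: net change also depends on exposure trends over 12 months. The entry rule is a cut-off among children who report exposure; nothing shows that it selects unusually high values.

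A reader might also infer that the trial will be judged by significance in the intervention arm alone, a pattern with probability at most 0.5 × 0.5 = 25% under no effect if the arms are independent. It is 0.864 × 0.136 = 12% in the 86% scenario, and no section adopts that rule.

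It is tempting to add that a paired test defeats intention to treat by dropping children without follow-up. A model for the single 12-month cotinine value drops them too, and handling of missing data may properly sit in a fuller document. Likewise, having only two time points is no fault for cotinine, which is measured exactly twice.

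**Conclusion.** The point stands in its plain form: the stated Phase 2 test does not compare the randomised arms, so it cannot answer the effectiveness question. This needs no numerical assumption.

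How far regression to the mean alone would mislead is unknown from the documents. The range runs from about nominal to 97%, depending on the share above the cut-off, the correlation, the scale of analysis and the skewness. It concerns cotinine only; the scores are exposed to ageing and repeat testing instead, for which no size can be given.

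The stated 90% power at effect size 0.3 is close to that of a two-sided within-arm paired test (88% to 91%) and well above that of an unadjusted two-sided between-arm test (61% to 66%). A reader might infer that the sample size was derived from the paired test. That is possible, but 250 is not reproduced exactly by it and the article does not say which test was used.

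**What to change.** Replace the Phase 2 sentence with a between-arm comparison that adjusts for the baseline value and accounts for the randomised cluster. One suitable form is a mixed model with arm, baseline and a random cluster effect, for 12-month cotinine and for the questionnaire scores at follow-up. The article gives no number of clusters, so provide for a small-sample correction if they are few. State the scale on which cotinine is analysed. Report the adjusted difference between arms with its 95% confidence interval, and keep paired t-tests as description only.

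No new measurements are needed; those already scheduled suffice. The cost lies in power, which must be restated for this comparison. Without adjustment, 90% power at effect size 0.3 needs 468 children, or 520 with attrition, before any cluster inflation. Baseline adjustment recovers part of the shortfall, by an amount that depends on a correlation the documents do not give. The sponsor should state that correlation and the clustering assumption, then either confirm that 250 is enough or state the power that 250 provides.
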